## INVESTIGATION SCHEDULE

| Study Periods                                    | Screening and Patient information | Consent (ICF) + inclusion | Intervention                          | Follow-up                            |
|--------------------------------------------------|-----------------------------------|---------------------------|---------------------------------------|--------------------------------------|
| Visit                                            | 0                                 | 1                         | 2-17 (max)                            | 18-19                                |
| Time (hour, day, week)                           | -2 to -1 day                      | 0                         | From inclusion day during max 15 days | ICU discharge and Hospital discharge |
| Inclusion and exclusion criteria                 | X                                 |                           |                                       |                                      |
| Patient or legal representative Information      | X                                 |                           |                                       |                                      |
| Patient or legal representative consent          |                                   | X                         |                                       |                                      |
| Randomisation                                    |                                   | X                         |                                       |                                      |
| Demographics                                     |                                   | X                         |                                       |                                      |
| Anthropometrics                                  |                                   | X                         | X                                     | X                                    |
| Details of hospitalisation                       |                                   | X                         |                                       |                                      |
| Diagnosis                                        |                                   | X                         |                                       |                                      |
| Medication                                       |                                   | X                         | X                                     |                                      |
| Laboratory Tests                                 |                                   | X                         | X                                     |                                      |
| Vitals                                           |                                   | X                         | X                                     |                                      |
| Severity score                                   |                                   | X                         |                                       |                                      |
| Glycaemia                                        |                                   |                           | X                                     |                                      |
| Events                                           |                                   |                           | X                                     |                                      |
| Energy and protein intake                        |                                   |                           | X                                     |                                      |
| Elimination                                      |                                   |                           | X                                     |                                      |
| Digestive tolerance                              |                                   |                           | X                                     |                                      |
| Physical therapy                                 |                                   |                           | X                                     | X                                    |
| (Serious) Adverse Events, Adverse device effects |                                   |                           | X                                     | X                                    |
| Device Deficiencies                              |                                   |                           | X                                     | X                                    |

\* The information reported during Visit 1 is the most recent information available at the time of this visit.

### **1.4 Laboratory**

No laboratory analysis will be requested during this study. Data recorded will correspond to the usual currently laboratory analysis requested in the clinical practice of the adult ICU of HUG. Therefore, analyses will be carried out by the laboratory collaborating with HUG.

### **1.6 Data Safety Monitoring Committee**

A data safety monitoring committee is not planned for this study. The purpose of the study is "safety and efficacy" of a new medical device. The study terminates in case of: ethical concerns; insufficient subject recruitment; if 5 patients present with two severe hypoglycaemias ( $\leq 2.2$  mmol/l) in the intervention group; 10 device deficiencies which prevent the use of Glucosafe 2 (GS2) for 4 hours; alterations in accepted clinical practice that make the continuation of the investigation unwise; early evidence of benefit or harm of the experimental intervention or because root mean square (RMS) prediction error of GS2 is greater than 26% for predictions of BG 2 hours into the future. Device deficiencies will be handled according to point 5.1 described in the GS2-IB.

## **1.7 Any other relevant Committee, Person, Organisation, Institution**

Not applicable.

## **2. ETHICAL AND REGULATORY ASPECTS**

The final positive decision of the CEC and of the CA on the conduct of the investigation will be made and given in writing to the Sponsor before the investigation can start. Additional requirements set by the authorities must be implemented.

### **2.1 Registration of the investigation**

This study is registered on the International Clinical Trial Registry website: [www.clinicaltrial.gov](http://www.clinicaltrial.gov). This registry is listed in the WHO international Clinical Trials Registry. ID: NCT03890432. The study will also be registered in the Swiss National Clinical Trials Portal (SNCTP).

### **2.2 Categorisation of the investigation**

Category C2 (study involving a medical device which does not bear a conformity mark yet) (Art.6 ClinO-MD) [4].

### **2.3 Competent Ethics Committee (CEC)**

The Sponsor-Investigator will submit the investigation to the CEC and obtain ethical committee approval before the start of the investigation. The PI ensures that approval from the CEC is obtained and filed in the Investigator site file before the investigation starts.

#### **2.3.1 Reporting duties to the Competent Ethics Committee**

Amendments are reported according to Art. 15 ClinO-MD [4] (See also 2.10).

The regular or premature end of the investigation as well as the interruption of the investigation is reported to the CEC within 15 days (within 24 hours if it is due to security reasons) (Art. 36 ClinO-MD). The reasons for a premature end or an interruption have to be explained.

A final report shall be submitted within one year after the regular end of the investigation and within 3 months after a premature end of the investigation (Art. 37 ClinO-MD) [4].

### **2.4 Competent Authorities (CA)**

The Sponsor-Investigator will submit the investigation to the CA and obtain regulatory approval before the start of the investigation. The PI ensures that approval from the CA is obtained and filed in the Investigator site file before the investigation starts.

#### **2.4.1 Reporting duties to the competent authorities**

Amendments are reported according to Art. 20 ClinO-MD [4] (see also 2.10).

The regular or premature end of the investigation as well as the interruption of the investigation is reported to the CEC within 15 days (within 24 hours if it is due to security reasons) (Art. 36 ClinO-MD) [4]. The reasons for a premature end or an interruption have to be explained. Refer to chapter 10 for safety reporting.

### **2.5 Ethical Conduct of the Investigation**

The investigation will be carried out according to the CIP and with principles enunciated in the current version of the Declaration of Helsinki [1], the European Regulation on medical devices 2017/745 (MDR) [5], the Norms ISO14155 [2] and ISO14971 [6], the ICH-guidelines of Good Clinical Practice (GCP) [3] as applicable, the Swiss Human Research Act (HRA) [7] and its Ordinances and Swiss regulatory authority's requirements [4, 8]. The CEC and the CA will receive the Annual Safety Report (ASR) and interim reports and be notified about investigation stop/end in agreement with local requirements.

### **2.6 Declaration of interests**

The sponsor and the HUG clinical investigators have no conflict of interest to declare in relation to this

clinical trial. The manufacturer, Aalborg University, is a public academic institution and does not receive financial support from private sources of any kind in support of this clinical trial. All rights to the device remain with Aalborg University for the duration of the trial. Public funding from a governmental fund has been received in January 2021, and the contract with the funding organization requires Aalborg University to investigate ways to commercialize the device in the future. On that basis it is declared that the manufacturer, Aalborg University, has a commercial interest in this clinical trial.

## **2.7 Patient Information and Informed Consent**

The investigators explain to each subject the nature of the investigation, its purpose, the procedures involved, the expected duration, the potential risks and benefits and any discomfort it may entail. Each subject and/or legal representative is informed that the participation in the investigation is voluntary and that he/she may withdraw from the investigation at any time and that withdrawal of consent will not affect his/her subsequent medical assistance and treatment. The subjects and/or legal representatives are informed that he/she can ask any question, and consult with family members, friends, their treating physicians or other experts before deciding about their participation in the investigation. A deadline of 24 hours will be given to the legal representative or to the independent physician after presentation of the study to give or not their consent. For patients, once they are capable of consenting, a 48-hour delay after presentation of the study will be given.

The subjects/ legal representatives are informed that authorised individuals other than their treating physician may examine his/her medical records.

All subjects and/or legal representative are given a subject information sheet and a consent form describing the investigation and providing sufficient information for the subjects to make an informed decision about their participation in the investigation.

The formal consent of a subject/ legal representative or doctor not associated with the study, using the approved consent form, is obtained before the subject is submitted to any investigation procedure.

The subject/ legal representative should read, understand, and voluntarily agree before signing and dating the informed consent form, and is given a copy of the signed document. The consent form is signed and dated by the subject and the PI (or her/his designee). The signed consent form is retained as part of the investigation records.

As this study involves patients in an emergency situation, most patients will be unable to give their informed consent at the time of inclusion. Nevertheless, participants should provide their own consent as soon as they regain their capacity to consent, in order to confirm their agreement for the continuation of their participation in the study.

The consents' procedure for participants to intervention or control group will be carried out as follows:

- 1) It will be ensured that the patient did not express his/her right to refuse to participate in research projects in any identifiable manner (electronic patient's record or according to relatives). This information will be clearly documented in the patient's medical files.
- 2) If the patient has his capacity to discern, he/she will give his/her own consent before inclusion in the study.
- 3) If the patient is unable to consent at the inclusion time, the consent will be obtained from their legal representatives in a proxy consent. Waiting for the legal representative consent, a doctor not associated with the study is called to safeguard the interests of the person concerned (art 30 HRA [7]. The enrolment of the patient in the study can be made when the independent physician authorisation is obtained. This authorisation form must be signed by the independent physician and an investigator of the study and will be retained as part of the study records.
- 4) As soon as the patient has recovered his/her capacity to consent, he/she will be asked to sign a post-hoc consent form, which will be retained as part of the study records.

### **2.7.1 Request for authorization under Article 34 of the HRA**

For the participants in the retrospective control group, we ask for permission to use the data without the patient's consent in accordance with Article 34 of the HRA [7]. In fact, we want to analyse 71 data files from patients who were admitted to the ICU within 2 years before the start of the study. The process of obtaining post-hoc consent would be extremely complex as ICU mortality can be as high as 20%. The exclusion of patients for whom we cannot obtain consent would lead to a selection bias.

The project sponsor/investigator confirms that no patient health-related data will be utilized in this study from patients that refused participation (in written or documented oral refusal) in research studies.

Important information regarding informed consent and the use of collected data:

- If the participant or representative refuses post-hoc or proxy consent, the participant will be withdrawn from the study. The data collected so far will be destroyed and will not be analysed (ClinO Art. 17, alinea 3) [8]. If a participant or representative withdraws his/her consent, the same process will apply.
- If no representative is identified and no proxy consent could be obtained, the patient will be withdrawn from the study and his/her data will be destroyed and will not be analysed. If the patient recovers his/her capacity to consent and declines to give consent, he or she will be withdrawn from the study and the procedure outlined above will apply.
- If a participant already enrolled in the study dies before consent or refusal could be obtained from him/ her or a representative, the personal health information collected may be used only if the participant has consented to the use of his/her personal health data for research purposes in an advance directive or other form.

## **2.8 Subject privacy and confidentiality**

The investigators affirm and upholds the principle of the participant's right to privacy and that they shall comply with applicable privacy laws. Especially, pseudo anonymity of the participants shall be guaranteed when presenting the data at scientific meetings or publishing them in scientific journals.

Individual subject medical information obtained as a result of this study is considered confidential and disclosure to third parties is prohibited. Subject confidentiality will be further ensured by utilising subject identification code numbers to correspond to treatment data in the computer files.

For data verification purposes, authorised representatives of the Sponsor, the CA or a CEC may require direct access to parts of the medical records relevant to the investigation, including subjects' medical history.

## **2.9 Early termination of the investigation**

The Sponsor may terminate the investigation prematurely according to certain circumstances, for example:

- Ethical concerns
- Insufficient subject recruitments
- More than 5 patients with two episodes of severe hypoglycaemia ( $\leq 2.2$  mmol/l) in the intervention group
- 10 device deficiencies that prevent the use of GS2 for 4 hours
- Changes in accepted clinical practice that are too large and make it unwise to continue the investigation
- Early evidence of benefit or harm of the experimental intervention
- Root mean square (RMS) prediction error of GS2 is greater than 26% for predictions of BG 2 hours into the future (see point 3.4 for rationale)

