### 3.7 Risk evaluation (Risk-to-Benefits rationale)

A device risk analysis and risk assessment has been conducted according to EN ISO 14971. Risks were identified by class: General risks, software risks, usability risks and installation risks according to EN 14971, EN62304, EN62366-1 and EN14971, respectively. All identified risks related to the four events: Hypoglycaemia, hyperglycaemia, overfeeding or underfeeding. After mitigation of risks, all risks were minor, except two general risks, GR2 and GR3, both related to hypoglycaemia. These two risks therefore require justification.

The justification of **GR2**, as stated in the GS2-Risk Management Report, showed that the expected risk of a patient experiencing hypoglycaemia is 2%, which is smaller than the 5% reported in IIT trials in the control group and much smaller than what is reported for the intervention group. The risk of 2% depends on the setting Hypoglycaemia Risk Maximum (GS2- SDS03-Settings in Appendix 7.2). The Hypoglycaemia Risk Maximum is set to 0.05%. This is the risk that a given BG measurement, made at the due time calculated by GS2, is hypoglycaemic, as described in GS2-SDS06-BG prediction error and BG due time. Assuming an average of 40 BG measurements per patient, then the patients risk of hypoglycaemia can be estimated as  $0,05\% \cdot 40 = 2\%$ .

The justification of GR3, as stated in the GS2-Risk Management Report, showed that the occasional hazard of not recognizing a type 1 diabetes patient is outweighed for that patient by the expected medical benefit of using GS2.

The final Risk Management Report in the GS2-Risk Management File state that the GS2 software has a Class B safety classification and that after all possible efforts to mitigate risks only two unacceptable risks remained, both general risks and both justifiable.

Moreover, as GS2 only gives advice and cannot control directly the insulin management, the risk remains lower than with an autonomous software.

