## **6. CLINICAL INVESTIGATION DESIGN**

### **6.1 General clinical investigation design and justification of design**

This study is an unblinded randomized controlled trial that aims to evaluate the performance and the safety of a new bedside tool: GS2 in comparison to the standard of care.

Data from the historical control group will be analysed retrospectively for 71 patients hospitalized in the ICU at the same period within 2 years before the study. The historical control group is included for two reasons. The first is to be able to assess cross-over effects. These may happen in the randomized control group, if the caregiver's behaviour in this group is influenced by the caregiver's exposure to the GS2 system, when the caregiver is using the system in the intervention group.

The second reason is to confirm the predictive accuracy of GS2. As described in section 3.3.1 there are modest differences between the prediction errors estimated from the three patient cohorts previously analysed with Glucosafe. It is therefore appropriate to confirm that the prediction error of GS2 is similar or smaller compared to Glucosafe's. In case the prediction error is smaller, it will be possible to reduce the frequency of blood glucose measurements, as described in IB 2.5 "Mechanisms of action". The frequency of blood glucose measurements is one of the outcomes for workload (section 9.2.3). This reduces workload and the amount of blood drawn from the patient. In case the prediction error is larger, it is a reason for discontinuation or modifications of the intervention, as noted in Section 2.9.

The analysis of data from the historical control group will start as soon as the authorization of the study has been obtained. Enrolment for the intervention and control groups will start when the retrospective analysis of the historical control group has been completed. Enrolment is expected to take 8 months. The data and the results will then be analysed and submitted for publication.

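### Sections 1.6 and 2.9 set different counts and different force for the severe-hypoglycaemia stop, and both allow a stop for early benefit although no interim analysis is planned

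*Protocol*

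**What the plan says.** Section 1.6 of the protocol states that "A data safety monitoring committee is not planned for this study" and then lists the circumstances in which the study *terminates*. One is "if 5 patients present with two severe hypoglycaemias" (2.2 mmol/l or lower) in the intervention group. Another is "early evidence of benefit or harm of the experimental intervention".

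Section 2.9 repeats the list with a different opening: "The Sponsor may terminate the investigation prematurely according to certain circumstances", followed by words that mark the list as examples. Here the hypoglycaemia item reads "More than 5 patients with two episodes of severe hypoglycaemia", with the same glucose limit and the same group. The item "Early evidence of benefit or harm of the experimental intervention" appears again.

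Section 11.3, headed as the statistical criteria for terminating the investigation, describes only when an individual patient's follow-up ends. Section 11.4.4 plans no interim analyses. Section 6.1 states that "This study is an unblinded randomized controlled trial".

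**The concern.** The glucose limit, the two episodes per patient and the treatment group are identical in the two sections, so they describe one rule. At exactly five qualifying patients, section 1.6 calls for a stop, while section 2.9 has not reached its listed threshold, although it does not forbid stopping. Reading section 1.6 as at least five does not remove the difference.

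This is the only numerical stop that counts harmed patients; the others count device deficiencies or measure prediction error. With no monitoring committee, the sponsor applies the rule to its own trial. Section 3.4 reports no clinical testing of the device, and section 10.3.1 calls this its first study in humans. Sections 2.10 and 2.11 prohibit waivers and restrict deviations, so a monitor or inspector would need to know which text binds.

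The benefit wording is a separate matter. Harm can emerge from continuing safety reports without a formal analysis. Benefit on time in target can be judged only by comparing the arms, and the protocol provides no look, boundary or body for that. In an unblinded trial, informal looks at accumulating results are possible, and a stop on an unadjusted look would raise the false-positive rate.

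**Working it through.** **Inputs from the protocol.** 71 intervention patients (section 11.2). Trigger at 5 (section 1.6) or at 6, meaning more than 5 (section 2.9). Section 3.7 says "the expected risk of a patient experiencing hypoglycaemia is 2"%, obtained as 0.05% per measurement × 40 measurements.

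**Assumptions.** The protocol gives no rate for two severe episodes in one patient. The calculations assume independent episodes, the same risk for every patient and exactly 71 patients exposed.

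**1. Under the protocol's own risk.** Treat all hypoglycaemia as severe, with a Poisson mean of 0.02 episodes per patient.

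- P(two or more) = 1 − e^(−0.02) × (1 + 0.02) = 0.000197.
- Expected qualifying patients = 71 × 0.000197 = 0.0140.
- P(at least 5 of 71) = 3.9 × 10⁻¹²; P(at least 6 of 71) = 8.4 × 10⁻¹⁵.

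Neither version would trigger.

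**2. At assumed rates p of patients with two severe episodes.** Binomial(71, p):

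| p | P(≥5), section 1.6 | P(≥6), section 2.9 | Difference = P(exactly 5) |
|---|---|---|---|
| 2% | 1.4% | 0.3% | 1.1 points |
| 5% | 28.2% | 14.4% | 13.8 points |
| 10% | 85.0% | 72.6% | 12.4 points |

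**3. How wrong the 0.05% would have to be.** First find the p that gives the stated chance of meeting the rule in 71 patients. Then find the per-measurement risk r for which P(Binomial(40, r) ≥ 2) = p.

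| Chance of meeting the rule | Count | p | r | r ÷ 0.0005 |
|---|---|---|---|---|
| 5% | 5 | 0.0282 | 0.00652 | 13.0 |
| 5% | 6 | 0.0374 | 0.00762 | 15.2 |
| 50% | 5 | 0.0655 | 0.01044 | 20.9 |
| 50% | 6 | 0.0795 | 0.01168 | 23.4 |

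**4. Early benefit.** The planned design has one final two-sided 5% test, so false superiority is 2.5%. The number of looks is not in the protocol and is assumed here: equally spaced looks, an early stop only for benefit at z > 1.96, and otherwise the two-sided final test.

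- One extra look at half the information (correlation √0.5, bivariate normal): two-sided type I error = 1 − P(z₁ ≤ 1.96, |z₂| ≤ 1.96) = 6.66%. False superiority = 1 − P(z₁ ≤ 1.96, z₂ ≤ 1.96) = 4.16%.
- Five looks in total (4 million simulated trials): 9.6% and 7.1%.
- If the single extra look were itself two-sided, type I error would be 8.3%.

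**The case against.** The strongest reply is that the mismatch changes almost nothing. Section 2.9 is an open list under a permissive verb, so a sponsor who stops at the fifth patient, as section 1.6 requires, breaches nothing. Ethical concerns or harm allow a stop at any count. Serious events reach the sponsor-investigator within 24 hours (section 10.3.2). The device's advice is checked daily in the run-in and, if acceptable, weekly afterwards (section 7.2.1). All of this stands and limits the consequence. It does not settle which text binds a sponsor who wishes to continue at five.

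A second reply is that the verb in section 1.6 also governs items that need judgement, such as ethical concerns, and so cannot make the whole list automatic. That is fair for those items. A count of patients needs no such judgement, so the proposed change is confined to that one rule.

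A third reply is that the type I error figures describe looks the protocol excludes. That is correct, and they are illustrations whose size depends on the assumed looks. The inconsistency remains: the protocol names benefit as a ground for stopping and provides no means of judging it.

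Finally, the binomial and Poisson figures ignore clustering of repeat episodes within patients. The 0.05% applies to measurements made at the software's due time and is not tied to 2.2 mmol/l. Replacement of withdrawn patients (section 11.2) could expose more than 71. These points also stand: the figures show scale and are not forecasts.

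**Conclusion.** The concern holds. The current text gives two counts and two degrees of obligation for one safety stop, and it lists early benefit as a ground for stopping without any planned comparison to support it.

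The size is modest. Under the protocol's stated risk the rule is not reached under either version. The choice of count matters only if that risk is badly wrong, by roughly 13 to 23 times under the assumptions above; in the assumed range of 5% to 10% of patients, it moves the chance of triggering by 12 to 14 percentage points. But a safety stop exists for the case in which the expected risk is wrong, and here no independent committee is planned to resolve the ambiguity.

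The sample size and the planned single final test are unaffected. Only an actual early stop for benefit on unadjusted looks would inflate the error rate. The point should be fixed, but it does not undermine the design.

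**What to change.** State one count for the severe-hypoglycaemia stop in sections 1.6 and 2.9, for example 5 patients, the stricter figure already in section 1.6. Use the same mandatory verb for that rule in both places; the items that need judgement can remain discretionary. In both sections, delete benefit from the item on early benefit or harm and keep harm, which brings the lists into line with section 11.4.4.

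The cost is protocol wording only, with no change to the sample size, data collection or analysis.

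### The only numerical hypoglycaemia criterion counts patients with two severe episodes each, so it is insensitive to an excess of severe hypoglycaemia unless recurrence within patients is common

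*Protocol*

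**What the plan says.** Protocol 2.9 gives as one ground for stopping "More than 5 patients with two episodes of severe hypoglycaemia" in the intervention group, severe meaning at or below 2.2 mmol/l. The list opens with "The Sponsor may terminate the investigation prematurely according to certain circumstances, for example", so it is discretionary and not exhaustive. Protocol 1.6 states the criterion as "if 5 patients present with two severe hypoglycaemias" and says that the study terminates when it is met.

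Both sections also list "Early evidence of benefit or harm of the experimental intervention" and ethical concerns, with no event, threshold or time of review attached. The remaining criteria concern recruitment, device deficiencies that prevent use for 4 hours, changes in practice, and the prediction error at 2 hours. Section 1.6 plans no data safety monitoring committee and 11.4.4 plans no interim analysis.

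Section 3.7 justifies the residual hypoglycaemia risk by stating that "the expected risk of a patient experiencing hypoglycaemia is 2%, which is smaller than the 5% reported in IIT trials in the control group". Section 10.3.1 describes the trial as the first evaluation of the device in humans, with the incidence of anticipated device effects not yet known.

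**The concern.** The counted unit is a patient with two severe episodes. All 71 intervention patients could have one severe episode each and the count would still be zero. Whether the rule reacts to an excess therefore depends on how often severe episodes recur within a patient, on which the protocol gives no figure. It also gives neither a reason for the two-episode unit nor the rule's trigger probabilities.

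At stake is the protection of patients during enrolment. With no committee and no planned look at accumulating data, a cumulative excess of single severe episodes would meet no stated numerical criterion. Any response would depend on someone noticing a pattern across individual reports.

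**Working it through.** **Inputs from the protocol.** Intervention patients: 71 (11.2). Patients with two severe episodes needed to trigger: 5 (1.6), or at least 6 because 2.9 says more than 5. Risk per measurement 0.05%, 40 measurements per patient, accepted risk per patient 2%, cited control-group figure 5% (all 3.7).

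**The protocol's own figure.** 0.0005 × 40 = 2.00%; exactly, 1 − (1 − 0.0005)^40 = 1.98%. The 2% is reproduced.

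**Trigger probability.** Let R be the proportion of patients with at least one severe episode and p2 the proportion with at least two. The rule triggers with probability P(X ≥ 5) or P(X ≥ 6), where X ~ Binomial(71, p2). All 71 patients are assumed to be observed, which is the most favourable point for the rule.

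**Recurrence (assumed, because the protocol gives no figure).**
- Independent (Poisson) episodes: λ = −ln(1 − R), p2 = 1 − exp(−λ)(1 + λ). At R = 10%, λ = 0.1054 and p2 = 0.0052.
- Negative binomial with k = 0.25, matched on the proportion with no episode. At R = 10%, p2 = 0.023, so about 23% of affected patients recur.
- Half of affected patients recur: p2 = R/2. At R = 10%, p2 = 0.05.

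**Results at R = 10%** (71 × 0.10 = 7.1 patients expected with an episode):

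| Recurrence | p2 | 5 patients (1.6) | More than 5 (2.9) |
|---|---|---|---|
| Independent | 0.0052 | 0.004% | 0.0002% |
| Negative binomial, k = 0.25 | 0.023 | 2.3% | 0.5% |
| Half recur | 0.05 | 28% | 14% |
| All recur (extreme) | 0.10 | 85% | 73% |

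Under independence only 71 × 0.0052 ≈ 0.37 patients are expected to have two episodes.

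**Other rates, 5-patient version.** At R = 5% with half recurring: 3.3% (0.9% for more than 5). At R = 15%: 0.16% independent, 26% negative binomial, 62% half recurring. At R = 20%: 1.8%, 70% and 85%. Under independence, an 80% chance of triggering needs R of about 40% (43% for more than 5).

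**Effect of the unit alone.** Applying the same counts to patients with at least one severe episode means X ~ Binomial(71, R):

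| R | at least 5 | at least 6 |
|---|---|---|
| 2% | 1.4% | 0.3% |
| 5% | 28% | 14% |
| 10% | 85% | 73% |

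At R = 10% the fall from 85% to between 0.004% and 28% comes entirely from requiring a second episode. This table is a comparison, not a proposed rule.

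**The case against.** Four objections have force.

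**Other safeguards exist.** Advice is reviewed daily in the run-in and weekly afterwards if acceptable (7.2.1). Advice that raises concern is refused, an investigator is contacted within 12 hours, and the PI decides on suspension (10.3.2). Serious adverse events and device deficiencies reach the sponsor within 24 hours, and serious device effects go promptly to the ethics committee and the authority. The list in 2.9 is open and includes early evidence of harm. A reader might infer that nothing else could stop the trial or that a first severe episode goes unnoticed; the documents do not support either. What stands is that these routes work case by case or by judgement, and none sets a cumulative number for hypoglycaemia.

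**Recurrence is unknown.** A reader might infer that the rule would almost never trigger at several times the accepted risk. That holds for low recurrence only. With half of affected patients recurring, a 10% rate triggers with probability 14% to 28%, and a 20% rate with 73% to 85%.

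**The benchmark differs.** The 2% and 5% in 3.7 concern hypoglycaemia with no stated threshold of 2.2 mmol/l. A reader might infer that the rule was meant to test the 2% and fails to do so, but the protocol never presents it as such a test. The calculation above therefore takes the severe-episode rate as its own variable. Nor would an untriggered rule mean that safety went unassessed: mild and severe hypoglycaemia are safety outcomes (5.4, 9.2.4).

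**Replacing the rule is a clinical decision.** This stands in full. The documents show an unreconciled criterion and an unstated operating characteristic; they do not show which stopping rule is right.

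**Conclusion.** The point holds in this form. The one criterion that puts a number on hypoglycaemia ignores a single severe episode in a patient, and it is insensitive unless recurrence is common. At a 10% rate of patients with any severe episode, its trigger probability runs from about 0.004% to 28% for 5 patients and from about 0.0002% to 14% for more than 5, as recurrence goes from independent episodes to half of affected patients. These figures rest on full observation of 71 patients and on assumed recurrence; higher recurrence would raise them further. The weakness is present under either count, so it is separate from the disagreement between 1.6 and 2.9 over the number of patients and over mandatory versus discretionary stopping. That disagreement also has to be resolved.

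**What to change.** 1. Reconcile 1.6 (5 patients, study terminates), 2.9 (more than 5, sponsor may terminate) and the risk justification in 3.7. State which hypoglycaemia threshold the 2% and 5% refer to, and give the reason for the two-episode unit. The choice of rule is the sponsor's.
2. State the trigger probabilities of the reconciled rule over a range of severe-episode rates and recurrence, as in the tables above.
3. Have the investigators keep a running tally of intervention patients with any severe episode, taken from the adverse-event entries made at the daily visits (9.3.3). At a count the sponsor chooses and justifies, it should prompt a review by the sponsor and PI, not automatic termination.

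The cost is amendment wording and a tally of data already recorded; no new committee is needed. The downside is some unnecessary reviews. For illustration only, a count of 5 would be reached by full enrolment with probability 1.4% at a true 2% rate and 28% at a true 5% rate, so the chosen count should be published with such figures.
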